### Recruitment {15}

Participants will be recruited from the Department of Orthopaedics and Traumatology at the Prince of Wales Hospital in Hong Kong. The orthopaedic surgeons will explain the details of the trial based on the eligibility criteria. They will screen all patients with Achilles tendinopathy coming for consultation in the outpatient department at the Prince of Wales Hospital. In addition, the information of the study will be sent to the coaches of the sports teams at CUHK. Recruitment information for the trial will also be sent through the internal mass mail system at CUHK. Individuals will come for eligibility assessment at the Sports Injury and Biomechanics Laboratory if they are interested to join the trial.

## Assignment of interventions: allocation

### Sequence generation {16a}

The randomisation is performed using an online research randomiser (https://www.randomizer.org/). Participants will be randomised into 1:1 allocation in a block of 10. Each allocation will be assigned a unique RFID generated by the chief engineer from Quantum TX and they will be recognisable by the PEMF machine.

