### Sample size {14}

A minimum clinically significant difference is 16 points on the VISA-A scores based on the pilot study using VISA-A as the primary outcome in treating AT [18]. It was reported in a feasibility study using another conservative treatment, laser therapy as an adjunct treatment to eccentric exercise therapy for AT. A total of 20 participants were recruited and VISA-A was the primary outcome. Significant improvements were shown in both treatment groups in VISA-A [18]. The power calculation to detect the minimum clinically significant difference is conducted using the G Power programme at a type I error of 5%, power of 80% (correlation value, 0.03; pooled SD, 20.25). Twenty subjects per group are obtained to detect a significant difference in VISA-A among two groups if a two-way repeated-measures analysis of variance (ANOVA) is proposed. It is expected to have a 20% dropout rate. Thus, the final study sample size is 40 subjects in total [19].

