## Statistical methods

### Statistical methods for primary and secondary outcomes {20a}

Statistical analysis will be performed using SPSS software (SPSS 26.0) based on the intention-to-treat principle. The normality of the data will be tested using the Kolmogorov–Smirnov test. A repeated-measures two-way analysis of variance (ANOVA) will be used to compare muscle strength, ankle range of motion, and results of questionnaires at baseline, 4 weeks, 8 weeks, and 3-, and 6-month follow-up. A nonparametric Mann–Whitney *U* test will be used to compare questionnaire results (ordinal data) between control and experimental groups. Subgroup analysis for participants with mid-portion or insertional AT will also be performed using interaction tests from ANOVA. Significant differences for each test measuring physical function will be based on an alpha level set at 0.05.

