### Methods for additional analyses (e.g. subgroup analyses) {20b}

The heterogeneity in tendinopathy will be addressed by sub-group analysis. AT will be categorised into midportion and insertional tendinopathy. The assessor will make the diagnosis of the type of Achilles tendinopathy. Midportion AT will be diagnosed by local thickening and a colour doppler flow of at least two out of four in the modified Öhberg score 2–6 cm proximal to the insertion of the Achilles tendon. Insertional AT will be diagnosed by local thickening and colour Doppler flow of at least grade two of four in the modified Öhberg score within 2 cm of the insertion of the Achilles tendon. Sub-group analysis will be performed to understand if PEMF has clinical effects on all outcome measures in the midportion tendinopathy and insertional tendinopathy, respectively, since the number of participants will be smaller in the subgroups. A non-parametric test, the Mann–Whitney *U* test, will be used to detect if there are significant differences in the outcomes for each subgroup.

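### Tendon site is the heterogeneity the plan names, but it is neither a stratification factor nor a term in the main VISA-A model, so chance imbalance between arms on site goes uncorrected

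*Protocol article*

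**What the plan says.** **Allocation.** Sequence generation {16a} describes one list: "Participants will be randomised into 1:1 allocation in a block of 10". No stratification factor is given there or under {16b} or {16c}.

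**Heterogeneity.** Section {20b} states that "The heterogeneity in tendinopathy will be addressed by sub-group analysis" and that "AT will be categorised into midportion and insertional tendinopathy". Site is defined by local thickening plus Doppler flow of at least grade 2 on the modified Öhberg score, either 2–6 cm above the insertion or within 2 cm of it. A Mann-Whitney U test "will be used to detect if there are significant differences in the outcomes for each subgroup".

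**Main analysis.** Section {20a} states that "A repeated-measures two-way analysis of variance (ANOVA) will be used to compare muscle strength, ankle range of motion, and results of questionnaires" across baseline and four follow-up visits. The factors are group and time; no covariate is listed. The same section adds a Mann-Whitney test for questionnaire scores, which has no place for a covariate.

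**Where site does enter a model.** Section {20a} also says: "Subgroup analysis for participants with mid-portion or insertional AT will also be performed using interaction tests from ANOVA". So {20a} and {20b} give two different methods for the same subgroup question.

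**When site is known.** Table 1 requires structural change on ultrasound at the initial examination. Section {20b} says the assessor makes the site diagnosis, but not when. Table 2 places the graded ultrasound outcomes at Week 1, after allocation.

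**The concern.** The plan singles out one patient characteristic as important and then uses it in neither of the two places where it could protect the overall comparison: the allocation list and the primary model. A subgroup analysis does not do that work. It asks whether the effect differs by site; it leaves the overall estimate unadjusted.

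With 20 per arm, a noticeable imbalance on a two-level factor is common. If the sites respond differently to eccentric exercise, an imbalance moves the VISA-A contrast in a direction unrelated to PEMF. A reader of the results table would see the imbalance and have no prespecified adjusted estimate to turn to.

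**Working it through.** **Inputs from the protocol article:** 40 participants, 20 per arm, blocks of 10; target difference 16 VISA-A points; SD 20.25; five visits. All 40 are taken as analysed, because {20c} plans multiple imputation.

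**Inputs not in the article (assumptions):** insertional share p, taken from 20% to 50%; a difference between sites of 10 VISA-A points, for illustration.

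**The plan's own figure.** The article gives no figure for the site split or for imbalance. Its only sizing figure is 20 per arm. A two-sample normal formula with a one-sided 5% test returns it: 2 × (1.645 + 0.842)² × (20.25/16)² = 19.8, rounded up to 20. A two-sided test gives 2 × (1.960 + 0.842)² × (20.25/16)² = 25.1, so 26. That is a separate matter; 20 per arm is taken as given here.

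**Step 1: chance of imbalance.** If each participant is insertional with probability p, independently of arm, the difference in insertional counts between arms has variance 40p(1−p). With a continuity correction, P(difference ≥ 4) ≈ 2[1 − Φ(3.5/√(40p(1−p)))]. A 30,000-run simulation of four blocks of 10 agrees:

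| p | √(40p(1−p)) | formula | simulation, ≥ 4 | simulation, ≥ 6 |
|---|---|---|---|---|
| 20% | 2.53 | 16.7% | 16.7% | 2.9% |
| 30% | 2.90 | 22.7% | 22.3% | 5.6% |
| 40% | 3.10 | 25.9% | 25.7% | 7.4% |
| 50% | 3.16 | 26.8% | 26.8% | 7.9% |

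The chance for a fixed number of insertional cases can be checked by hand. With exactly 8 of 40, P(6:2 or worse) = 2 × [C(20,6)C(20,2) + C(20,7)C(20,1) + C(20,8)] / C(40,8) = 18,081,540 / 76,904,685 = 23.5%.

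**Step 2: effect on the contrast.** A difference of 4 cases is 4/20 = 0.20 of an arm, so the contrast moves by 0.20 times the site difference. If the sites differ by 10 points in VISA-A change, that is 2 points:
- 2/16 = one-eighth of the target difference.
- The standard error of a single-visit comparison is 20.25 × √(2/20) = 6.4, and 2/6.4 = 0.31 of a standard error.

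The site difference that matters is one in change. The ANOVA includes baseline as a visit, so a constant difference in level between sites cancels from the group-by-time contrast.

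**Step 3: precision to be gained.** A 10-point site difference accounts for p(1−p) × 10² of the variance. Taking 20.25 as the SD of the quantity compared (variance 410), that is 16/410 = 3.9% at p = 20% and 25/410 = 6.1% at p = 50%.

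**Step 4: the subgroup tests.** Simulated power of an exact two-sided Mann-Whitney test at 16 points and SD 20.25 is about 9% at 4 v 4, 19% at 6 v 6, 35% at 10 v 10 and 49% at 14 v 14. The interaction test addresses the right question but is not powerful either. With 4 v 4 insertional and 16 v 16 midportion, the standard error of the difference in effects is 20.25 × √(1/4 + 1/4 + 1/16 + 1/16) = 16.0. A difference in effect as large as the whole target would then be only one standard error.

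**The case against.** Unstratified permuted blocks are a valid design, and whether to stratify 40 people is a judgement. Chance imbalance is already allowed for in the standard error. A covariate list is often left to a full protocol or SAP, which is not shown. The 10-point site difference is assumed, and even so the shift is about 0.3 of a standard error. The article does not say that site predicts VISA-A. All of this stands, and it limits the point to a cheap improvement. What remains is that the article does state how site will be handled, and that method does not protect the main comparison.

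Four stronger readings are tempting, and the documents do not support them:

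- **That the analysis ignores site.** It does not: {20a} puts site in an ANOVA interaction test. Only the main comparison lacks it.
- **That the primary comparison is biased.** Randomisation keeps it unbiased on average; a given allocation may be unlucky.
- **That missing stratification makes the insertional comparison impossible to win.** At 6:2 the smallest exact two-sided p is 2/28 = 0.071, against 2/70 = 0.029 at 4:4. But this is mainly a matter of subgroup size. With 7 or fewer insertional cases no split reaches 0.05, stratified or not; with 10 the risk is 0.8%. Averaged over a random number of cases, stratifying lowers the risk only from 49% to 43% at a 20% share and from 23% to 18% at 25%. It also applies only to exact p-values, which the article does not specify; the uncorrected asymptotic p at 6:2 is 0.0455.
- **That allocation should now be restratified.** Stratifying would cut the chance of a difference of 4 or more to about 1%, but enrolment began in July 2021. Changing the allocation scheme part-way through a 40-person trial is a debatable trade for something that a model term largely provides.

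**Conclusion.** The point holds as a modest weakness in the primary analysis. Site is named as the heterogeneity to address, yet it is absent from the allocation scheme and from the main VISA-A model. Under an assumed insertional share of 20% to 50%, a difference of 4 or more insertional cases between arms has about a 17% to 27% chance, and each such difference shifts the contrast by at least 0.20 times the site difference in VISA-A change. The loss is in precision and credibility; the validity of the trial is not in question. The imbalance figures rest on the assumed share, and the size in points rests on a site difference that the article does not give.

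The within-site Mann-Whitney tests are a weak basis for any statement about site. Their power stays below 50% even at 14 v 14, and comparing significance in one site with non-significance in the other does not test whether the effect differs.

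**What to change.** 1. **Primary model.** Prespecify tendon site and its interaction with time as terms in the VISA-A model for all 40 participants, however many are already enrolled. The interaction with time is needed because only a site difference in change affects the group-by-time contrast.
2. **Classification.** Take site from the eligibility or baseline scan, before the first treatment session and blind to allocation, and record when this is done. State a rule for participants who meet neither definition in {20b}, since Table 1 requires only structural change, and for those with a different site in each leg, since bilateral disease is allowed.
3. **Site question.** Reconcile {20a} and {20b} by relying on the interaction test. Report the difference in effect with a confidence interval, and present within-site results as descriptive.

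**Cost.** Site takes 1 degree of freedom (between-participant error falls from 38 to 37). Site by time over five visits takes 4 more (within-participant error falls from 38 × 4 = 152 to 37 × 4 = 148). A third category for unclassifiable participants would add to this. No new data collection and no change to the allocation list or the RFID cards is needed.

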### Concealment mechanism {16b}

The randomisation is performed using an online research randomiser by the chief engineer at Quantum TX. He will only share the randomisation results with the biostatistician at the Chinese University of Hong Kong. It will not be disclosed to the participants and assessors of this trial before the end of the treatment period. The participants will be assigned a unique RFID by which the PEMF or sham treatment will be randomly assigned to the RFID. Participants and assessors are blinded as participants will use the RFID to complete the treatment without knowing the treatment they receive.

### Implementation {16c}

The chief engineer from Quantum TX performs the randomisation. The randomisation result is shared with the biostatistician at the Chinese University of Hong Kong. The orthopaedic surgeon and PhD candidate from CUHK recruit participants. The PhD candidate will complete the assessment and assigns participants to interventions. The randomisation results will only be disclosed to the orthopaedic surgeon and PhD candidate after the participants complete all PEMF sessions.

## Assignment of interventions: blinding

### Who will be blinded? {17a}

Assessors and participants will be blinded to the interventions. Participants will be blinded to the PEMF given to them as active and sham PEMF will not produce heat or other perceivable sensations. The engineer performs the randomisation from Quantum TX, and it will not be disclosed to the assessors before the end of the PEMF treatment period.

### Procedure for unblinding if needed {17b}

There will be unblinding of the participants and assessors if a severe adverse event occurs. The adverse event will be reported to the Joint Clinical Research Ethics Committee of the Chinese University of Hong Kong and the New Territories East Cluster of the Hospital Authority.

## Data collection and management

### Plans for assessment and collection of outcomes {18a}

The collection of demographic data will be done during screening and before recruitment. Participants that fulfil all the inclusion criteria will be randomised into PEMF or sham groups. Follow-up assessments with various outcome parameters will be conducted with data processing details as shown in the section “Outcomes {12}”.

### Plans to promote participant retention and complete follow-up {18b}

Participants will choose the time for each PEMF session during the week. The working hours will be extended to the evenings so that participants may come for assessment and treatment after work.

### Data management {19}

All data collected will be entered into the online database in Excel files and SPSS files. All data will be kept in password-protected computers and destroyed 5 years after publication in PhD thesis and peer-reviewed journals. The PhD candidate will be responsible for data collection, data entry, and data analysis. She will enter the data into the database for screening and randomisation purposes. After data collection, she will enter all data into Excel files and then input them into SPSS files for data analysis. Double data entry and range checks for data values will be used to promote data quality.

### Confidentiality {27}

All personal information and consent forms will be stored in locked cabinets at the Sports Performance and Biomechanics Laboratory. The online electronic database with personal information will be kept on password-protected computers. All data collected will be kept strictly confidential and only accessed by members of the trial team. Participants will not have the right to access the data set. There is no plan to share the data collected with other organisations.

### Plans for collection, laboratory evaluation, and storage of biological specimens for genetic or molecular analysis in this trial/future use {33}

Not applicable. This study will not require the use of biological specimens.

## Statistical methods

### Statistical methods for primary and secondary outcomes {20a}

Statistical analysis will be performed using SPSS software (SPSS 26.0) based on the intention-to-treat principle. The normality of the data will be tested using the Kolmogorov–Smirnov test. A repeated-measures two-way analysis of variance (ANOVA) will be used to compare muscle strength, ankle range of motion, and results of questionnaires at baseline, 4 weeks, 8 weeks, and 3-, and 6-month follow-up. A nonparametric Mann–Whitney *U* test will be used to compare questionnaire results (ordinal data) between control and experimental groups. Subgroup analysis for participants with mid-portion or insertional AT will also be performed using interaction tests from ANOVA. Significant differences for each test measuring physical function will be based on an alpha level set at 0.05.

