### Outcomes {12}

#### Patient-reported outcomes

The primary outcome is the score of the Victorian Institute of Sports Assessment-Achilles (VISA-A) questionnaire, which is explicitly designed for Achilles tendinopathy. VISA-A will be used to evaluate pain and symptom severity with activity in participants with AT. Chinese-speaking participants will complete the validated VISA-A HK questionnaire [8]. The VISA-A questionnaire covers three domains associated with AT: pain, function, and sporting activities. A deterioration in self-reported pain, function, and sporting activities is the critical reason patients with AT come for medical consultation. Improving questions covered in VISA-A is often the rehabilitation goal for these patients. Since PEMF was used for pain reduction for other musculoskeletal disorders, similar effects may be applied to patients with AT.

Short Form-36 questionnaires (SF-36) will be used to evaluate health-related quality of life [9]. PEMF may reduce pain levels and allow participants to resume social activities, recreational activities, and functional tasks at work. A numeric pain rating scale (NPRS) will be used to assess the level of pain on the categories “general on the day of review,” “family and responsibility at home,” “recreation,” “social activities,” and “running training or other physical activities.” Each NPRS ranges from “no pain” to “severe pain”.

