### Participant timeline {13}

Table 2 is used to demonstrate the schedule of enrolment, interventions, assessments, and visits for participants.

**Table 2 Tab2:** Participant timeline

	Study period						
	Enrolment	Allocation	Post-allocation				
Timepoint	Before allocation	0	Week 1	Week 4	Week 8	3 months	6 months
Enrolment:							
Eligibility screen	X						
Informed consent	X						
Allocation		X					
Interventions:							
Control group: Sham PEMF plus eccentric exercise			X	X	X		
Experimental group: Active PEMF plus eccentric exercise			X	X	X		
Assessments:							
Self-reported questionnaires (NPRS, VISA-A, SF-36)			X	X	X	X	X
Functional outcomes (AROM, heel-rise)			X	X	X	X	X
Ultrasonographic outcomes (Tendon thickness, neovascularity, tendon elasticity)			X	X	X	X	X

*AROM* Ankle range of motion, *NPRS* Numeric pain rating scale, *SF-36* Short-form 36, *VISA-A* Victorian Institute of Sports Assessment-Achilles

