### Methods in analysis to handle protocol non-adherence and any statistical methods to handle missing data {20c}

The intention-to-treat analysis will be used to include all study participants in the groups to which they are randomised, regardless of any departures from the original assigned group. The missing values will be estimated by multiple imputations with the assumption that values are missing at random.

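### Baseline VISA-A is analysed as one of five outcome visits and the ANOVA term that tests treatment is not named; on either reading this costs efficiency, by an amount that depends on the correlation

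*Protocol article*

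**What the plan says.** The Outcomes section fixes the endpoint: "The primary outcome is the score of the Victorian Institute of Sports Assessment-Achilles (VISA-A) questionnaire". Statistical methods {20a} then states: "A repeated-measures two-way analysis of variance (ANOVA) will be used to compare muscle strength, ankle range of motion, and results of questionnaires at baseline". The sentence goes on to list the follow-ups, so the ANOVA covers "results of questionnaires at baseline, 4 weeks, 8 weeks, and 3-, and 6-month follow-up". VISA-A is one of those questionnaires, so its baseline value is the first of five levels of the time factor.

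The same section adds a Mann–Whitney U "test will be used to compare questionnaire results (ordinal data) between control and experimental groups", with no visit and no baseline adjustment stated. Nowhere does the protocol name a baseline covariate or a change score, or say whether the group effect or the group-by-time interaction is the treatment test. Sample size {14} speaks of a difference between the two groups, which leans towards the group effect without settling it.

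Sample size {14} gives the planning values: "A minimum clinically significant difference is 16 points on the VISA-A scores", and "correlation value, 0.03; pooled SD, 20.25". It arrives at 20 per group and expects 20% dropout.

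In Table 2 (Participant timeline {13}), the row that opens "Self-reported questionnaires (NPRS, VISA-A, SF-36" has its first mark at Week 1, under post-allocation, in the column where treatment also starts.

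**The concern.** Randomisation makes the expected difference between arms at baseline zero. A visit with no expected treatment difference adds nothing to the group contrast if it is treated as an outcome. The same measurement used as a covariate explains part of the follow-up variance and corrects for chance imbalance.

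The consequence depends on which term is the test:

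- **Group main effect:** the estimate averages one null visit with four informative ones, and a chance baseline gap carries partly into it.
- **Group-by-time:** the estimate is not averaged down, but a lasting difference is tested against a 4-df alternative that covers every possible pattern over time.

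With 40 participants, that efficiency matters. The baseline value is already collected, so using it better needs no new data.

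**Working it through.** **Inputs from the protocol.** Difference 16 points, SD 20.25, correlation r = 0.03, alpha 5%, 20 per arm. If the 20% dropout comes out of the 40, 16 per arm remain.

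**Assumptions.** Two-sided test; compound symmetry; true difference 0 at baseline and 16 at each of four follow-ups; r = 0.3, 0.5 and 0.7 tried beside the protocol's 0.03.

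**The protocol's own figure.** The 20 per group is not reproduced by a repeated-measures ANOVA with the stated inputs. With f = 16/20.25/2 = 0.395, r = 0.03 and five measurements, total N is 14 for the between-group test and 18 for the interaction. A two-sample comparison needs 26 per arm (normal) or 27 (t); only its one-sided normal form gives 20. The point here does not depend on this. It takes 20 and 16 per arm as given.

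**Dilution (group effect only).** (0 + 16 + 16 + 16 + 16)/5 = 12.8.

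**Imbalance (group effect only).** Given a baseline gap D and no treatment effect, each follow-up gap has expectation rD, so the five-visit mean shifts by (D + 4rD)/5 = (0.2 + 0.8r)D. The SD of D is 20.25 × √(2/20) = 6.4 points. A one-SD gap moves the estimate by 0.6 × 6.4 = 3.8 points at r = 0.5, and by 0.224 × 6.4 = 1.4 at r = 0.03.

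**Power formulas.** Each contrast has SE = √(V × 2/n), with power from the noncentral t:

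- Five-visit group effect: effect 12.8, V = SD²(1 + 4r)/5, df 38.
- Unadjusted mean of four follow-ups: effect 16, V = SD²(1 + 3r)/4, df 38.
- Baseline-adjusted mean of four: effect 16, V = SD²[(1 + 3r)/4 − r²], df 37.
- Baseline-adjusted single visit: effect 16, V = SD²(1 − r²), df 37.
- Interaction: noncentral F on 4 and 152 df. The centred differences are −12.8 and four times 3.2, with sum of squares 163.84 + 4 × 10.24 = 204.8, so λ = (20/2) × 204.8/[410.06(1 − r)] = 4.99/(1 − r).

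**Worked at r = 0.5, 20 per arm.**

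- Group effect: SE = 6.404 × √0.6 = 4.96; 12.8/4.96 = 2.58; power 0.711.
- Interaction: λ = 9.99; power 0.700.
- Unadjusted mean of four: SE = 6.404 × √0.625 = 5.06; 16/5.06 = 3.16; power 0.869.
- Adjusted mean of four: SE = 6.404 × √0.375 = 3.92; 16/3.92 = 4.08; power 0.978.
- Adjusted single visit: SE = 6.404 × √0.75 = 5.55; 16/5.55 = 2.89; power 0.802.

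**Full range.**

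| Per arm | r | Group effect, 5 visits | Interaction, 4 df | Mean of 4, unadjusted | Mean of 4, adjusted | Single visit, adjusted |
|---|---|---|---|---|---|---|
| 20 | 0.03 | 0.984 | 0.396 | 0.997 | 0.997 | 0.682 |
| 20 | 0.3 | 0.836 | 0.534 | 0.942 | 0.975 | 0.723 |
| 20 | 0.5 | 0.711 | 0.700 | 0.869 | 0.978 | 0.802 |
| 20 | 0.7 | 0.608 | 0.914 | 0.790 | 0.995 | 0.926 |
| 16 | 0.03 | 0.955 | 0.317 | 0.985 | 0.985 | 0.580 |
| 16 | 0.3 | 0.742 | 0.433 | 0.880 | 0.936 | 0.620 |
| 16 | 0.5 | 0.608 | 0.585 | 0.781 | 0.941 | 0.703 |
| 16 | 0.7 | 0.510 | 0.831 | 0.690 | 0.981 | 0.856 |

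At r = 0.5 and 20 per arm, removing baseline from the outcome visits takes power from 0.711 to 0.869, and the covariate takes it from 0.869 to 0.978. At r = 0.03 the covariate adds almost nothing.

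**The case against.** Several objections limit the point, and most of them stand in part.

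- **Validity.** A reader might infer that the planned test is invalid. It is not: under randomisation neither term is biased under the null (sphericity aside).
- **Dilution.** A reader might take the effect to be diluted whatever the test. The averaging to 12.8 and the imbalance weight apply only to the group effect. Under group-by-time, a baseline gap that stays constant over the visits drops out.
- **The protocol's own correlation.** At 0.03 the group effect loses about one percentage point (0.984 against 0.997). Only the interaction reading shows a large loss there, about 60 points. Whether 0.03 is realistic cannot be settled from the document, so the range has to be shown.
- **Adjusting at one visit.** A reader might expect any baseline-adjusted contrast to do better. A single visit does not: at 20 per arm it has 0.682 against 0.984 at r = 0.03, and 0.723 against 0.836 at r = 0.3. The protocol also names no primary visit.
- **Constant effect.** PEMF stops after 8 weeks, so the effect may fade. With an assumed profile of 8, 16, 12, 8 at r = 0.5 and 20 per arm, the adjusted mean has 0.780, the group effect 0.409 and the interaction 0.517. If the effect instead builds as 4, 8, 12, 16, the adjusted mean has 0.700 at r = 0.5 against 0.349 and 0.577. At r = 0.7 with that profile the interaction is marginally ahead (0.824 against 0.813), and the adjusted last visit beats the adjusted mean from r = 0.3 upwards (0.723 against 0.688).
- **Table 2.** A reader might infer that baseline is measured after a treatment session. The document does not say so: Trial design {8} names a baseline assessment separate from the follow-ups, and a shared column shows no order. The table is ambiguous, no more.

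**Conclusion.** The concern holds as one of efficiency and of an unnamed treatment term. For a constant 16-point follow-up effect, SD 20.25, compound symmetry and a two-sided 5% test, the baseline-adjusted mean of the four follow-ups has more power than either planned term at every correlation tried.

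The size is uncertain. Against the group effect at 20 per arm, the gain runs from about 1 percentage point at r = 0.03 to about 39 at r = 0.7 (0.995 − 0.608). Against the interaction it runs from about 60 points at r = 0.03 down to about 8 at r = 0.7 (0.995 − 0.914). A fading or slowly building effect lowers the absolute figures and, in one setting with high correlation, removes the advantage over the interaction.

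The change should be made, but the trial is not unsound without it.

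**What to change.** In Statistical methods {20a}, replace the repeated-measures ANOVA with a linear mixed model on the four post-baseline visits: arm, visit, arm-by-visit, the baseline value of the same outcome, and an unstructured covariance.

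Prespecify the arm contrast averaged over the four follow-ups as the treatment test for VISA-A, with its 95% confidence interval. Report single-visit contrasts as secondary, since their power is lower under a constant effect. If the team expects the effect to build or fade strongly, it should settle the contrast on that ground before the data are seen.

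The model uses participants with incomplete follow-up under the assumption the protocol already makes in {20c}: "The missing values will be estimated by multiple imputations with the assumption that values are missing at random".

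In Table 2, state that the baseline assessment precedes the first PEMF or sham session.

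The cost is a change of wording in the protocol or analysis plan. No extra data, visits or participants are needed.

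### The primary outcome VISA-A is given two unranked tests, a repeated-measures ANOVA and a Mann–Whitney test, with no deciding effect or visit named

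*Protocol article*

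**What the plan says.** All references are to the protocol article.

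- **Primary outcome (Outcomes {12}, patient-reported outcomes):** "The primary outcome is the score of the Victorian Institute of Sports Assessment-Achilles (VISA-A) questionnaire". No time point is attached.
- **First test (Statistical methods {20a}):** "A repeated-measures two-way analysis of variance (ANOVA) will be used to compare muscle strength, ankle range of motion, and results of questionnaires at baseline" and at four later visits, so five time points in all.
- **Second test (next sentence of {20a}):** a Mann–Whitney U "test will be used to compare questionnaire results (ordinal data) between control and experimental groups". No visit is named.
- **Normality (same section):** "The normality of the data will be tested using the Kolmogorov–Smirnov test". No rule follows on what the result changes.
- **Sample size {14}:** "Twenty subjects per group are obtained to detect a significant difference in VISA-A among two groups", on condition that a two-way repeated-measures ANOVA is proposed. The difference is 16 points, the type I error 5%, the power 80%, the correlation 0.03 and the pooled SD 20.25. Neither the effect tested nor the number of measurements is given.

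**The concern.** VISA-A is a questionnaire score, so both sentences of {20a} apply to it. The first treats it as a continuous score with means, the second as ordinal ranks. The reason given for the Mann–Whitney test is the type of data, not a failed normality test, so the two sentences do not read as alternatives.

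A two-way repeated-measures ANOVA yields a group effect and a group-by-time interaction. A Mann–Whitney comparison can be made at any of four follow-ups. If these disagree, someone must choose after seeing the results. Under {19} the PhD candidate analyses the data. Under {16c} the same person may learn the allocation once participants have completed their PEMF sessions, which is before the 3- and 6-month visits. An unranked choice is therefore harder to defend here than in a trial whose analyst stays blinded.

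What is at stake is the error rate behind a claim that PEMF improves VISA-A, and whether the test that decides is the one for which the trial was sized.

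**Working it through.** **1. Does the plan's own sample size show which effect was meant?**

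Inputs from {14}: difference 16, SD 20.25, correlation ρ = 0.03, alpha 5%, power 80%, 20 per group. Then d = 16/20.25 = 0.790 and f = d/2 = 0.395, so f² = 0.156. With N the total and m the number of measurements, the G*Power noncentrality formulas are:

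- group effect: λ = N f² m / (1 + (m − 1)ρ)
- group-by-time interaction: λ = N f² m / (1 − ρ)

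Example: group effect, m = 2, N = 28 gives λ = 28 × 0.156 × 2 / 1.03 = 8.48 and power 80%, so 14 per arm. For m = 2 to 5 the required number per arm is:

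| Effect | Per arm, m = 2 to 5 |
|---|---|
| Group effect | 14 down to 7 |
| Interaction, f = d/2 | 14 down to 9 |
| Interaction, f = d/4 | 50 down to 31 |

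None gives 20, so the stated figure does not identify the effect. Whether 20 is correct is a separate matter on which this point does not depend.

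**2. Error rate if more than one route can carry the conclusion.**

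As a reference, k independent tests at 5% give 1 − 0.95^k: 9.75% for k = 2 and 26.5% for k = 6. The tests here are correlated, so null trials were simulated: 20 per arm, five visits, normal scores, equal correlation between visits, each test at two-sided 5%, 20,000 trials per correlation. The protocol gives only 0.03; the other correlations are assumptions to show the range. Each test alone rejected in 4.5% to 5.3% of trials.

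| Counts as success | ρ = 0.03 | 0.3 | 0.5 | 0.7 | 0.9 |
|---|---|---|---|---|---|
| t-test or Mann–Whitney, same visit | 5.9% | 5.5% | 5.9% | 6.3% | 5.8% |
| Interaction, or Mann–Whitney at one visit (week 8) | 8.9% | 8.6% | 9.0% | 9.7% | 9.3% |
| Interaction, or Mann–Whitney at any of four follow-ups | 19.8% | 18.7% | 18.1% | 17.0% | 13.7% |
| Group effect, interaction, or Mann–Whitney at any of four | 22.1% | 19.9% | 18.7% | 17.3% | 14.0% |

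In a separate run of 5,000 trials per correlation, the two ANOVA effects alone gave 10.1%, 9.8% and 10.5% at ρ = 0.03, 0.5 and 0.7.

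The first row shows that swapping a parametric test for a rank test at one fixed visit costs little. Most of the inflation comes from leaving the effect and the visit open.

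**3. Power of a single-visit contrast.**

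d√(n/2) = 0.790 × √10 = 2.50, and 2.50 − 1.96 = 0.54, which gives about 70% by the normal approximation. The two-sided t-test gives 68% with all 20 per arm observed, and 80% power needs 27 per arm. Baseline adjustment at ρ = 0.03 multiplies the SD by √(1 − 0.03²) = 0.9995, which gains nothing.

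**The case against.** - **The ANOVA is in effect designated.** Section {14} is the only place that ties a test to VISA-A by name, and that test is the repeated-measures ANOVA, which {20a} also lists first. This has weight: a reader might infer that no test is singled out at all, and the text does not support that. But the wording in {14} is conditional and names no effect, and {20a} then adds a second test without ranking it.
- **Mann–Whitney may be meant only for ordinal items such as the pain scale, or only if normality fails.** Either is possible, but {20a} states neither. Its wording covers questionnaire results without exception.
- **Visit and effect can be left to an analysis plan that is not shown.** Silence on those two would not by itself be a finding in a journal article. Two unranked assignments for the primary outcome in consecutive sentences are a conflict in the text, and an analysis plan would have to override one of them.
- **An error rate near 20% is not established.** A reader might infer it from the last two rows of the table. They require Mann–Whitney at every follow-up and success on any one result, and the article contains no such rule. They are a worst case.
- **A 5% level for every VISA-A test is not stated.** The sentence in {20a} reads "Significant differences for each test measuring physical function will be based on an alpha level set at 0.05", which names physical function. The 5% for VISA-A comes from {14}, for one ANOVA calculation. Applying it to each route is an inference.
- **Mann–Whitney cannot be set against 16 points.** True, but minor: the repeated-measures data still yield group means that can.

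**Conclusion.** The point holds as a conflict in the stated plan: two unranked tests for the primary outcome, with no deciding effect or visit. Section {14} leans towards the ANOVA but does not settle it.

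The size is conditional on more than one route being allowed to support the conclusion. It is then about 8–10% instead of 5% for the interaction or Mann–Whitney at one visit, and at most about 17–22% in the worst case for correlations 0.03 to 0.7 (14% at 0.9). These figures assume normal scores, equal correlations, complete data and 5% per test. The interim look at the primary endpoint {21b} is not included. One designated test would bring the rate back to about 5%.

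**What to change.** In {20a}, state that the primary VISA-A analysis is the repeated-measures model named in {14}, with one pre-named deciding effect or contrast at two-sided 5%. Examples are the between-arm difference in mean VISA-A at one pre-named visit, or averaged over follow-up, taken from that model. Report it with a 95% CI to set against the 16 points. Remove Mann–Whitney for VISA-A, or label it a sensitivity analysis that cannot change the conclusion. Label the other effects and visits secondary. Week 8, the end of the PEMF course, is one option; nothing in the article makes it the required one.

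The cost is wording, through the amendment route in {25}, and it should be settled before unblinded data are analysed. The sponsor gives up the alternative routes to a positive claim. There is also a power cost: a single-visit contrast has about 68% power at 20 per arm, not the 80% in {14}. The power statement must be recalculated for whichever contrast is chosen.
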